# The RESPITE trial: remifentanil intravenously administered patient-controlled analgesia (PCA) versus pethidine intramuscular injection for pain relief in labour: study protocol for a randomised controlled trial

**DOI:** 10.1186/s13063-016-1708-3

**Published:** 2016-12-12

**Keywords:** Remifentanil, Pethidine, Epidural, Pain relief, Labour, Childbirth

## Abstract

**Background:**

The commonest opioid used for pain relief in labour is pethidine (meperidine); however, its effectiveness has long been challenged and the drug has known side effects including maternal sedation, nausea and potential transfer across the placenta to the foetus. Over a third of women receiving pethidine require an epidural due to inadequate pain relief. Epidural analgesia increases the risk of an instrumental vaginal delivery and its associated effects. Therefore, there is a clear need for a safe, effective, alternative analgesic to pethidine. Evidence suggests that remifentanil patient-controlled analgesia (PCA) reduces epidural conversion rates compared to pethidine; however, no trial has yet investigated this as a primary endpoint. We are, therefore, comparing pethidine intramuscular injection to remifentanil PCA in a randomised controlled trial.

**Methods/design:**

Women in established labour, requesting systemic opioid pain relief, will be randomised to either intravenously administered remifentanil PCA (intervention) or pethidine intramuscular injection (control) in an unblinded, 1:1 individual randomised trial.

Following informed consent, 400 women in established labour, who request systemic opioid pain relief, from NHS Trusts across England will undergo a minimised randomisation by a computer or automated telephone system to either pethidine or remifentanil. In order to balance the groups this minimisation is based on four parameters; parity (nulliparous versus multiparous), maternal age (<20, 20 < 30, 30 < 40, 40+ years), ethnicity (South Asian (Pakistani/Indian/Bangladeshi) versus Other) and induced versus spontaneous labour.

The effectiveness of pain relief provided by each technique will be recorded every 30 min after time zero, until epidural placement, delivery or transfer to theatre, quantified by Visual Analogue Scale. Incidence of maternal side effects including sedation, delivery mode, foetal distress requiring delivery, neonatal status at delivery and rate of initiation of breastfeeding within the first hour of birth will also be recorded.

Maternal satisfaction with her childbirth experience will be determined by a postpartum questionnaire prior to discharge from the delivery ward.

**Discussion:**

The RESPITE trial’s primary outcome is the proportion of women who have an epidural placed for pain relief in labour in each arm.

**Trial Registration:**

Current Controlled Trials registration number: ISRCTN29654603. Registered on 23 July 2013.

**Electronic supplementary material:**

The online version of this article (doi:10.1186/s13063-016-1708-3) contains supplementary material, which is available to authorized users.

## Background

*Why is there a need to determine epidural conversion rates for intervention with remifentanil patient-controlled analgesia or pethidine for pain relief in labour?*

Childbirth can be extremely painful and the provision of pain relief during labour is a humanitarian duty and a vital component of a positive maternal experience. The majority of women who deliver in modern obstetric units choose a pharmacological method of pain relief, including Entonox (50% N_2_O and 50% O_2_ mixture), the injection of opioids or neuraxial analgesia by epidural placement. The commonest opioid used in labour is pethidine, administered by intramuscular (im) injection [1]. However, the effectiveness of pain relief provided by pethidine has long been challenged [2]. Its shortcomings are more serious when set against known side effects including maternal sedation, nausea and potential transfer across the placenta to the foetus [3]. More than a third of women who receive pethidine subsequently require an epidural due to inadequate pain relief [4]. Epidurals provide highly effective pain relief, but increase the risk of a forceps or suction delivery [5–7]. Instrumental deliveries are associated with various long-term disadvantages including increased likelihood of faecal incontinence [8], sexual dysfunction [9, 10] and extended hospital stay. Modern ‘low-dose’ epidural regimens reduce this impact on labour but do not completely mitigate the effect.

Patient-controlled analgesia (PCA) comprises drug administration via an intravenous drip with a small dose given each time a woman presses a button, giving her control over her own pain relief. The pump is programmed to ensure that the maximum dose allowable is within the safe range in a given time period. This form of delivery of pain relief matches the drug dose to pain sensation within the relevant time frame, which is not possible using a single-dose im injection [11]. Whilst PCA is in widespread use for acute pain relief after surgery it has only a limited role in obstetrics.

Remifentanil is a novel synthetic opioid with a very rapid onset (blood-brain equilibration 1.2–1.4 min) and short duration of action (context specific half-life 2–3 min) [12], giving it an analgesic profile which potentially makes it effective for providing pain relief over one to two uterine contractions after a single intravenously administered dose. It is subject to rapid redistribution and metabolism by nonspecific blood and tissue esterases, negating the potential for accumulation in mother or foetus [13]. Administration of remifentanil by PCA has been investigated in several small studies in comparison to pethidine and been shown to provide useful, although not complete, pain relief in labour [14–16]. Thus far, there is no evidence of detrimental neonatal effects in comparison to other opioids [13, 15, 17].

Many UK units offer this form of pain relief in cases where pain relief is requested, but an epidural is contraindicated, for example, in the case of maternal blood clotting abnormality or platelet dysfunction. However, the use of remifentanil PCA is not currently widespread or routine [18]. Crucially, there is some evidence from the studies performed thus far that the proportion of women who require rescue pain relief with an epidural after remifentanil PCA is reduced in comparison to pethidine [13], although no study has yet investigated this as a primary endpoint. If such an effect were proven and remifentanil demonstrated to be at least as safe and effective as pethidine, the number of women requiring an epidural in labour could potentially be reduced with a concomitant beneficial reduction in instrumental vaginal delivery [5–7] and its associated morbidity.

Numerous clinical studies have examined the effectiveness of pain relief in labour provided by remifentanil PCA. These studies have resulted in the refinement of dose administration techniques to provide the optimum balance between effectiveness and maternal safety.

An additional table file (see Additional file 1: Table S1) summarises the pertinent remifentanil studies to date and gives details on study size, comparator and the rate of conversion to epidural analgesia, if reported. The heterogeneity of dosing regimen and the opioid techniques used for comparator are immediately apparent; however, a degree of consistency in epidural conversion rate in direction and proportion emerges. It is notable that the only study which reported a higher epidural conversion rate with remifentanil used a substantially smaller drug dose than those in more recent studies [16]. Thus, inadequate pain relief may have influenced maternal decisions to request neuraxial blockade.

Epidural conversion rates of approximately 10% (range 5% to 19%) are commonly reported after remifentanil PCA regimens using bolus doses of 40 μg or equivalent. This compares to conversion rates of greater than 30% (range 17% to 39%) being representative in women receiving pethidine. A systematic review [19] conducted in 2011, included two studies [4, 20] reporting epidural conversion rates for remifentanil as half that for pethidine, with two other studies [16, 21] showing no difference in progression to epidural.

## Methods

### Aim

The primary aim of the RESPITE trial is to determine whether remifentanil PCA, administered for pain relief in childbirth, reduces the requirement for progression to epidural analgesia relative to pethidine im injection. Secondary questions regarding the relative effectiveness of pain relief, maternal and neonatal indices of wellbeing and maternal satisfaction will be addressed.

### Trial design

RESPITE is a randomised, open-label, multicentre trial comparing intravenously administered remifentanil PCA with pethidine im injection in women in established labour requesting systemic opioid pain relief.

#### Primary outcome

The primary outcome is the proportion of women who have an epidural placed for pain relief in labour in each arm after randomisation. This does not include regional block (spinal or epidural) sited specifically for the purpose of emergency caesarean section.

#### Secondary outcomes

The effectiveness of pain relief provided by each technique, quantified by Visual Analogue Scale taken every 30 min after time zero, until epidural placement, delivery or transfer to theatreThe incidence of maternal side effects, up to the end of 3rd stage of labour, including:◦ Excessive sedation score (not rousable by voice, sedation score of ≥4)◦ Oxygen saturation (pulse oximetry) <94% whilst breathing room air◦ Nausea requiring antiemetic administration◦ Requirement and indication for supplemental oxygen◦ Respiratory depression (respiratory rate below eight breaths/min)
Delivery mode (spontaneous vaginal, instrumental vaginal, caesarean section)Incidence of foetal distress requiring deliveryNeonatal status at delivery:◦ Apgar score at 5 min◦ Incidence of foetal acidosis determined by umbilical cord gas analysis (if performed)◦ Requirement for neonatal resuscitation◦ Incidence of, and indication for, admission to neonatal care
Rate of initiation of breastfeeding within the first hour of birthMaternal satisfaction with childbirth experience determined by postpartum questionnaire prior to discharge from the delivery ward

### Setting

Women will be recruited from multiple (fewer than 10) NHS trusts across England. Sites are able to participate in RESPITE if a care pathway is present which allows eligible women delivering at the site to be randomised between remifentanil and pethidine.

### Eligibility criteria

Women who are admitted to labour ward who fulfil all the following inclusion criteria and none of the exclusion criteria will be eligible to be randomised:

#### Inclusion criteria

16 years of age or olderBeyond 37 + 0 weeks’ gestationIn established labour, defined as regular painful contractions, irrespective of cervical dilatation, with vaginal birth intendedAble to understand all information (written and oral) presented (using an interpreter if necessary) and provide signed consentNot participating in any other clinical trial of a medicinal productLive, singleton pregnancy with cephalic presentationRequesting systemic opioid analgesia

#### Exclusion criteria

Contraindication to epidural analgesiaContraindication to im injectionHistory of a previous adverse reaction to pethidine or remifentanilPatients taking any long-term opioid drug therapy including methadoneSystemic opioid pain relief in the last 4 h administered by intravenous or intramuscular injection. (Medications administered per os comprising opioids alone or in combination preparations, administered in this 4-h period, are permitted)

#### Assessment of eligibility

Under the principles of Good Clinical Practice (GCP), the decision as to whether a patient is eligible for entry into a trial is considered to be a medical decision and, therefore, must be made by a medically qualified doctor. In the RESPITE study, this decision can be made by an anaesthetist or an obstetrician, but it is acknowledged that physicians are not routinely present when a woman requests opioid analgesia. The responsibility for eligibility assessment can be delegated to a research midwife or nurse and this decision will be made at a site level following local risk assessment in relation to the site’s organisation and practice, and should form part of the feasibility assessment for site approval. Eligibility for participation will be ratified by a GCP-trained physician.

### Randomisation

Randomisation will be carried out via a web-based central service (with staffed telephone back-up during office hours) based at Birmingham Clinical Trials Unit (BCTU). A 24-h, 7-day, interactive, telephone-based randomisation service will also be provided by the Health Services Research Unit at the University of Aberdeen. The web-based central service is only available to those named on the delegation log, whereas both telephone services are also available to clinical midwives, nurses and operating department practitioners (ODPs).

To obtain a randomised allocation and trial number, the person performing the randomisation process will need to verify a woman’s date of birth, confirm that all eligibility criteria have been met and provide the minimisation variables. At randomisation a confirmatory email will be sent to the randomising investigator, the local principal investigator (PI) and the research midwife/nurse. A ‘minimisation’ procedure using a computer-based algorithm will be used to avoid chance imbalances in parity, an important prognostic variable, which will be considered as an ordinal variable.

Minimisation variables will be:Parity: nulliparous versus multiparousMaternal age: <20, 20 < 30, 30 < 40, 40+ years.Ethnicity: South Asian (Pakistani/Indian/Bangladeshi) versus OtherInduced versus spontaneous labour

The procedures for randomisation will be fully documented and tested prior to the start of the trial and monitored by BCTU.

### Pain relief

Women will be randomly allocated in a 1: 1 ratio to either:Remifentanil PCA (intervention group) orIntramuscular injection of pethidine (control group)

#### Remifentanil

A dedicated intravenous cannula for remifentanil administration will be inserted into the woman ’s hand or forearm. The PCA pump will be preprogrammed by anaesthetic staff with a regimen to provide a bolus of 40 μg remifentanil with a lockout interval of 2 min. This dose regimen is based on sample guidelines adapted from those used in the introduction of remifentanil PCA into clinical practice in some UK labour wards [22] and reflects those used in the largest study up to 2010–2011 [20, 23]. In the event of excess sedation being recorded by regular observation of respiratory function, the regimen will be altered by reduction of the remifentanil bolus dose to 30 μg with a lockout interval of 2 min.

#### Pethidine

Pethidine will be delivered at a dose of 100 mg by im injection, up to 4-hourly in frequency, up to a maximum of four doses, making the maximum dose 400 mg in 24 h.

#### Intrapartum care

After the administration of analgesia, women will receive one-to-one midwifery care independent of group allocation. Clinical observations will be recorded every 30 min for both monitoring of the women’s status and for trial purposes, including respiratory rate, continuous oxygen saturation monitoring by pulse oximetry, numerical sedation score (on a scale of alert to unresponsive) and pain, using a Visual Analogue Scale pain score of 0 to 100.

The time at which active labour (regular painful contractions and more than 3-cm cervical dilatation) and second stage (dilatation of at least 10 cm) is diagnosed by vaginal examination, will be recorded but the degree of dilatation is not relevant to determination of eligibility.

Indications for contacting a physician anaesthetist are excessive sedation (not rousable by voice), a respiratory rate below eight breaths/min or oxygen saturation <94% despite supplemental inspired oxygen therapy

Women are free to request epidural pain relief at any point after trial entry. Neither the consenting physician, research midwife/nurse nor ODP will advise, offer opinion or be involved with a decision to proceed to epidural. The decision will be taken by a woman participating in the study supported by attending clinical (nonresearch) midwifery staff responsible for their care, if required. A maternal request for epidural analgesia will be treated according to local labour ward practice including assessment by attending midwifery and anaesthetic staff. The precise details of epidural technique will be dictated by local labour ward protocols. In the rare instance of epidural placement being recommended for medical indications arising during labour, this will be recorded. There is no reason to expect an imbalance of such an event between allocated groups.

Once effective epidural pain relief is established, the administration of opioid drugs will be discontinued irrespective of trial group allocation. Maternal observations will be recorded up to the point of epidural placement, delivery or transfer to operating theatre. Neonatal status will be recorded at delivery.

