### Statistical analysis

#### Sample size

Epidural conversion rates of approximately 10% (range 5% to 19%) are commonly reported after remifentanil. This compares to conversion rates of greater than 30% (range 17% to 39%) being representative in women receiving pethidine. Taking a deliberately conservative estimate of intervention effect using these data, a reduction in epidural conversion from 30% (pethidine) to 15% (remifentanil PCA) is reasonable. To detect such a reduction with 90% power at *p* = 0.05, would require 161 women in each arm of the trial, yielding a sample size of 322 in total. Adjustment must also be made to account for attrition of the study population as labour progresses. A proportion of the women will require urgent delivery, by caesarean section, for foetal indications before a request for further analgesia can be made. Assuming that this will not represent more than 25% of the sample after randomisation (reflecting the national caesarean section rate) and a 15% emergency caesarean rate is more realistic, a further 48 women will be recruited to offset this attrition of participants who are not capable of reaching the primary outcome. Allowing for a modest unavailability of primary outcome data and nonadherence of 6%, a total sample size of 400 is, therefore, proposed.

A detailed analysis plan will be developed and agreed by the TSC and the DMEC. Demographic factors and clinical characteristics will be summarised with counts (percentages) for categorical variables, mean (standard deviation) for normally distributed continuous variables, or median (interquartile or entire range) for other continuous variables.

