#### Primary analysis

The primary analysis will be a comparison of the management policies assigned at randomisation (intention-to-treat population.) The risk of the primary outcome in the remifentanil PCA group will be compared with the group and tested for significance at the two-sided 5% level of significance. In addition to the primary unadjusted analysis, a log-binomial model will be used to account for the minimisation variables. Risk ratios and 95% confidence intervals will be estimated. As the remifentanil PCA will generally only be available within the context of the RESPITE trial, we do not anticipate many protocol deviations; however, a limited incidence of nonadherence is predicted. The most likely cause is rapidly progressing labour with delivery occurring after randomisation, before allocated pain relief can be administered.

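### The adjusted log-binomial model leaves out stage of labour at randomisation, although a usable marker of it is recorded; adding the marker is a small, cheap gain, not the repair of an error

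*Protocol article*

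**What the plan says.** All places are in the protocol article.

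- **Entry.** The inclusion criteria define established labour by regular painful contractions, whatever the dilatation. Intrapartum care repeats this. For active labour (contractions and more than 3 cm) and for second stage, the time at which each "is diagnosed by vaginal examination, will be recorded but the degree of dilatation is not relevant to determination of eligibility".
- **Outcome.** Under Primary outcome, the endpoint is an epidural placed for pain relief in labour after randomisation. Intrapartum care lets women ask for one at any time after entry.
- **Analysis.** Under Primary analysis: "In addition to the primary unadjusted analysis, a log-binomial model will be used to account for the minimisation variables". The Randomisation section lists those variables as parity, maternal age, ethnicity, and induced versus spontaneous labour.
- **Progress of labour.** On the expected cause of nonadherence, Primary analysis says: "The most likely cause is rapidly progressing labour with delivery occurring after randomisation, before allocated pain relief can be administered". The statement is qualitative and concerns nonadherence.

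**The concern.** The labour still to come after randomisation is the window in which an epidural can be placed. A woman randomised early may have hours in which to ask for one, while a woman close to birth has little time. Stage at entry is therefore a plausible predictor of the primary outcome, and the trial records something close to it. The protocol does not leave the adjustment set open: it names the four minimisation variables, and none describes progress of labour.

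Two things follow if stage is prognostic. The adjusted risk ratio is somewhat less precise than the recorded data allow. And a chance difference between the arms in stage is neither limited by minimisation nor corrected in any stated analysis, which invites a post hoc argument if one is seen.

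**Working it through.** **1. The plan's own figure.** Inputs from Sample size and Primary analysis: "a reduction in epidural conversion from 30% (pethidine) to 15% (remifentanil PCA) is reasonable"; "To detect such a reduction with 90% power"; "tested for significance at the two-sided 5% level of significance". Allocation is 1:1 (Pain relief).

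With pooled variance under the null and mean risk 0.225:

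n per arm = [1.960·√(2·0.225·0.775) + 1.2816·√(0.30·0.70 + 0.15·0.85)]² / 0.15² = (1.1575 + 0.7445)² / 0.0225 = 160.8, so 161.

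This matches the protocol: "would require 161 women in each arm of the trial, yielding a sample size of 322 in total". Power at 161 per arm is 90.0% with no covariate.

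**2. Assumptions.** The documents give neither the share of women in active labour at randomisation (q) nor the effect of stage on epidural use. I take q from 30% to 70%, and the risk ratio for epidural, not yet active versus active (R), from 1.0 to 2.5. R is the same in both arms, and the arm risks are held at 30% and 15%.

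**3. Formula.** In an arm with risk p, the risk is p/(q + (1−q)R) for women in active labour and R times that for the others. The between-stage variance B in each arm is the part of p(1−p) that the covariate explains. For the risk difference, per-arm variance falls from V0 = Σp(1−p) = 0.21 + 0.1275 = 0.3375 to V1 = V0 − ΣB + C/2, where C is the variance of the stage-specific risk differences.

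**4. Worked case, q = 50%, R = 2.0.**
- Pethidine risks 20% and 40%, B = 0.0100. Remifentanil risks 10% and 20%, B = 0.0025.
- Stage-specific differences 10 and 20 points, C = 0.0025.
- V1 = 0.3375 − 0.0125 + 0.00125 = 0.32625, which is 3.3% lower.
- Women per arm for 90% power: 161 × 0.9667 = 155.6, so 156. Power at 161 per arm: 91.0%.
- Log risk ratio: variance × n falls from 0.70/0.30 + 0.85/0.15 = 8.00 to 0.20/0.09 + 0.125/0.0225 = 7.78, which is 2.8% lower.

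**5. Range.**

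| q | R | Lower variance (risk difference) | n per arm | Power at 161 |
|---|---|---|---|---|
| 50% | 1.0 | 0% | 161 | 90.0% |
| 50% | 1.5 | 1.2% | 160 | 90.4% |
| 50% | 2.0 | 3.3% | 156 | 91.0% |
| 50% | 2.5 | 5.5% | 153 | 91.6% |
| 30% | 2.5 | 3.4% | 156 | 91.0% |
| 70% | 2.5 | 6.7% | 151 | 91.9% |

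The last row is the largest gain in the range: 161 − 151 = 10 women per arm, and a 2.8% narrower confidence interval for the log risk ratio.

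**6. Beyond parity.** The adjusted model already holds parity, so the fair comparison is parity against parity plus stage. This was simulated with 4,000 trials per case, stratified Mantel-Haenszel tests, 161 per arm, and assumed values of 60% nulliparous, parity risk ratio 1.8 and q = 50%. Power went from 90.9% to 90.6% (R = 1.0), 90.5% to 90.9% (1.5), 90.7% to 92.0% (2.0) and 90.9% to 92.3% (2.5). Monte Carlo error is about 0.5 points.

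**7. Imperfect measurement.** Suppose 30% or 50% of women in active labour had not been examined before randomisation and so count as no. In the worked case, yes then covers 35% or 25% of women and the pethidine risk among the rest is 35.4% or 33.3%. B in the pethidine arm drops from 0.0100 to 0.0054 or 0.0033, the variance reduction from 3.3% to 1.8% or 1.1%, and power is roughly 90.4% to 90.6%.

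**8. Chance imbalance.** With q = 50% and 200 per arm, the difference between arms in the share in active labour has SD √(2·0.25/200) = 0.05. A 2-SD imbalance is 10 points. In the worked case the stage gap in risk is 20 points on pethidine and 10 on remifentanil, 15 on average, so the risk difference shifts by 0.10 × 15 = 1.5 points against a planned 15.

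**The case against.** The best defence is that nothing here is wrong. An unadjusted primary comparison, supported by a model with the minimisation variables, is valid and conventional, and the planned power is met without stage. A detailed analysis plan is still to be agreed and could add covariates. All of that stands, except that the protocol does name the adjustment set, so the omission is a stated choice.

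The covariate is also weaker than it looks. The protocol does not say that women are examined before randomisation or that dilatation at entry is recorded. A reader might infer that every woman has a clean baseline stage, but a no would mix women not in active labour with women not yet examined. A cut at 3 cm also puts a woman at 4 cm with one near full dilatation. Both points stand and shrink the gain; neither introduces bias, because the value is fixed before allocation.

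A reader might go further and want the primary test stratified by stage. The documents do not support that as a needed correction: it would tie the primary result to one unminimised, examination-dependent factor while the four minimisation variables stay in the supporting model. Nor is chance imbalance a separate flaw of the primary test, since its 5% level and confidence interval already allow for it.

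**Conclusion.** The point holds in a limited form. The adjusted model omits a recorded marker that plausibly relates to time at risk for the primary outcome. If stage predicts epidural use, the adjusted estimate forgoes about 0 to 7% of variance, equivalent to 0 to 2 power points or 0 to 10 women per arm. This rests on the assumed ranges (30% to 70% in active labour, stage risk ratio 1.0 to 2.5) and on correct measurement of stage; late examination cuts it further.

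Two stronger readings should be resisted. One is that the primary comparison is biased or underpowered: it is neither, since 161 per arm gives 90.0% power unadjusted. The other is that precision is certainly being lost, or that tens of women are at stake: the documents give no figure for the effect of stage, and a saving of about 45 of 400 women needs a five-fold risk ratio between stages (pethidine risks of 50% and 10%).

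**What to change.** In the Primary analysis section, or in the detailed analysis plan, prespecify active labour diagnosed before randomisation (yes/no) as one further baseline covariate in the adjusted log-binomial model, alongside the four minimisation variables. Derive it only from diagnosis times earlier than randomisation; a later diagnosis is not a baseline value and counts as no. State that no includes women not yet examined. Keep the unadjusted primary comparison as it is.

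The cost is one sentence and one model parameter, with no change to randomisation or recruitment. The data collection form should be checked to confirm that it captures diagnosis times falling before randomisation. The downside is that the covariate measures stage only approximately, which reduces the gain without biasing the comparison. If stage proves not to be prognostic, the expected power cost is negligible.

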### Follow-up

The study is primarily confined to the time period when a woman is in childbirth. Women enter the study from the time that they request opioid pain relief in labour and remain in the study for the duration of labour until both mother and baby have been discharged from hospital.

The period is, therefore, measured in days. Active data collection will only occur up to the point of child birth. There will be a single maternal contact thereafter to administer a brief questionnaire which includes metrics of maternal satisfaction. Mean stay in hospital after spontaneous vaginal delivery is 1–2 days. This period can be extended if delivery by emergency caesarean section has been required.

The trial schema which includes eligibility criteria and outcome measures is shown in Additional file 2: Figure S1.

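### Maternal side effects are defined to the end of the third stage, but the observations behind three of them stop at epidural, birth or theatre

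*Protocol article*

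**What the plan says.** All references are to the protocol article.

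- **Secondary outcomes** lists the "incidence of maternal side effects, up to the end of 3rd stage of labour". The five items are excessive sedation, oxygen saturation below 94% on room air, nausea needing an antiemetic, supplemental oxygen, and a respiratory rate below eight. The pain score, listed just before, has its own and earlier end: epidural, birth or theatre.
- **Intrapartum care** says: "Clinical observations will be recorded every 30 min for both monitoring of the women’s status and for trial purposes". It names respiratory rate, oxygen saturation, sedation score and pain score. It then says: "Maternal observations will be recorded up to the point of epidural placement, delivery or transfer to operating theatre". On treatment it says: "Once effective epidural pain relief is established, the administration of opioid drugs will be discontinued irrespective of trial group allocation".
- **Follow-up** keeps women in the study until mother and baby are discharged, but adds: "Active data collection will only occur up to the point of child birth". It continues: "There will be a single maternal contact thereafter to administer a brief questionnaire which includes metrics of maternal satisfaction".
- **Sample size** plans on the basis that "a reduction in epidural conversion from 30% (pethidine) to 15% (remifentanil PCA) is reasonable".

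**The concern.** The stop that Secondary outcomes attaches to the pain score alone is applied in Intrapartum care to all maternal observations. The third stage comes after birth, so the observation rule never reaches the end of the side-effect window. It falls further short in a woman who has an epidural or goes to theatre.

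Two things are at stake. Sites that follow one section will collect different data from sites that follow the other. Also, epidural placement is the primary outcome and is expected to differ between arms, so the length of observation would differ by arm too. A comparison of incidence over unequal windows is distorted even when the true risks are equal. The Background makes the case for remifentanil conditional on its being at least as safe as pethidine, so these outcomes matter although they are secondary.

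**Working it through.** **1. Which outcomes are affected.** Sedation, oxygen saturation and respiratory rate are in the half-hourly set, and that set stops early. Antiemetic use and supplemental oxygen are treatments given and are not in the set. The conflict therefore bears on three of the five side effects. The third-stage gap applies to every woman in both arms; the epidural gap depends on arm.

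**2. The planned epidural rates.** Inputs from Sample size and Primary analysis: 30% v 15%, 90% power, two-sided 5%. The article's figure reproduces without continuity correction:

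n = [1.960 × √(2 × 0.225 × 0.775) + 1.2816 × √(0.30 × 0.70 + 0.15 × 0.85)]² / 0.15² = (1.1575 + 0.7445)² / 0.0225 = 160.8, so 161 per arm.

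With 400 women, 200 per arm, recording is cut short at epidural in 200 × 0.30 = 60 pethidine women and 200 × 0.15 = 30 remifentanil women.

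**3. Effect on the recorded risk ratio.** Let p be the epidural rate in an arm and f the share of events in epidural women that fall after placement. Assume equal true risk in both arms, the same risk in women with and without an epidural, and the same f in both arms. The share of events captured is 1 − p × f, and the recorded ratio (remifentanil/pethidine) is (1 − 0.15f) / (1 − 0.30f). The documents do not give f, so it is ranged.

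| f | Captured, pethidine | Captured, remifentanil | Recorded ratio (true 1.00) |
|---|---|---|---|
| 0.1 | 97.0% | 98.5% | 1.02 |
| 0.25 | 92.5% | 96.3% | 1.04 |
| 0.5 | 85.0% | 92.5% | 1.09 |
| 1 | 70.0% | 85.0% | 1.21 |

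For an assumed true risk of 10% and f = 0.5, the recorded risks are 10% × 0.85 = 8.5% and 10% × 0.925 = 9.25%.

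**4. The article's own ranges.** Sample size quotes 17% to 39% for pethidine and 5% to 19% for remifentanil. At 39% v 5% the ratio is 0.975/0.805 = 1.21 for f = 0.5 and 0.95/0.61 = 1.56 for f = 1. At 17% v 19% it is 0.905/0.915 = 0.99 and 0.81/0.83 = 0.98.

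**5. Adding theatre.** Sample size gives 15% as a realistic emergency caesarean rate. If 15% of women without an epidural also stop early (assumption), the early stops are 0.30 + 0.70 × 0.15 = 40.5% and 0.15 + 0.85 × 0.15 = 27.75%. At f = 0.5 the ratio is 0.861/0.7975 = 1.08, little changed.

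**6. Scale against sampling error.** At an assumed 10% risk with 200 per arm, SE(log RR) = √[2 × (1/20 − 1/200)] = 0.30. The 95% interval spans a factor of exp(1.96 × 0.30) = 1.8 each way.

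**The case against.** The strongest reply is that little is actually lost.

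- Only active collection ends at birth. Women stay in the study to discharge, and Data form confidentiality names hospital notes as a data source. A reader might infer that breastfeeding in the first hour, neonatal admission, antiemetic use and oxygen use go unrecorded. The documents do not support that, since all four may be recoverable from notes.
- A reader might also infer that third-stage and theatre events are lost altogether. Monitoring of all types of adverse event requires reporting on awareness, with no stop at epidural, theatre or birth.
- Opioid is discontinued once the epidural is effective, and the Background gives remifentanil a half-life of 2–3 min, so f may be well below 1.
- A distortion of 1.02 to 1.09 is small beside a confidence interval spanning a factor of 1.8. It also runs against the new drug, so it would not create false reassurance about it.

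Most of this stands, and it limits the point to three outcomes with a bias of unknown size. It does not remove the contradiction. Awareness-based reporting in an open-label trial does not replace scheduled observations as a source of equal ascertainment. Nor need the fall in opioid effect be equal: pethidine is given up to 4-hourly, so its effects may outlast placement more than those of remifentanil. With f assumed at 0.25 for pethidine and 0.05 for remifentanil, the ratio is (1 − 0.15 × 0.05) / (1 − 0.30 × 0.25) = 0.9925/0.925 = 1.07.

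The gap between placement and an effective epidural might be read as a period without clinical monitoring. The text concerns what is recorded and does not show that.

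**Conclusion.** The contradiction is certain, and nothing in the article resolves it: as written, sedation, oxygen saturation and respiratory rate cannot be ascertained to the end of the third stage. The cut-off depends on the primary outcome, so the observed windows differ by arm if the planned effect holds.

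The size of any bias is illustrative. At the design rates and equal true risk the recorded ratio is about 1.02 to 1.21, for f from 0.1 to 1, and it tends to make remifentanil look relatively worse. A reader might infer that under-recording is established as heavier in the pethidine arm. That rests on 30% v 15%, which is a design assumption; at 17% v 19%, both within the article's ranges, the imbalance slightly reverses. The documents do not support a claim that safety data as a whole are compromised.

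**What to change.** Reconcile Secondary outcomes with Intrapartum care, and say in Follow-up what active data collection covers and which items come from notes after birth. For the three observation-based outcomes, set one data-recording window and apply it identically in both arms. There are two ways:

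- collect the trial data to the end of the third stage irrespective of epidural; or
- redefine the three outcomes as ending at the earliest of epidural, birth or theatre, report them as such, and state that the window depends on the primary outcome.

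Under the second option, dividing events by hours observed would not by itself cure the problem, because stopping at epidural is informative and rates are comparable only under a constant hazard.

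This concerns what the trial records; no clinical monitoring schedule is proposed. The cost is protocol and form wording and a little extra data abstraction. The sample size does not change.
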